We will train 20 HSAs in three districts (n = 60) in the prototype psychosis detection and management system, to (a) screen for psychosis and engage with a management system, (b) provide community-based brief psychosocial interventions, and (c) use referral routes to consultations with a mental health specialist when the presentation is complex. This will situate the HSAs explicitly within a healthcare pathway and equip them with the knowledge and skills to support earlier detection and delivery of elements of care at the village level. We will train Research Assistants (RAs) to administer the Present State Examination gold-standard diagnostic interview as part of the WHO’s SCAN (WHO, 1997). This will be used to screen positive and negative cases (validation study). The RA will facilitate community-based psychosocial interventions for people who screen positive for psychosis. Inter-rate reliability of diagnosis and outcome measures at baseline will be established.

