#### Activities

*Intervention cohort study without controls / pre-post sequential group design*. The analysis of individual outcomes will use appropriate descriptive statistics to present the outcome in each district as well as the overall statistic for all three districts. The outcome data will be stratified by health equity indicators (sex, age category, urban/rural residence) and by drop outs and loss to follow up. A sample size of 150 will be sufficient to detect a pre-post improvement of 20% overall (across the four sub-scales) of the WHOQoL primary outcome measure with a power of 90% (alpha = 0.05). The data will have a three-level structure with repeated outcomes measures collected with individuals clustered within three separate assessment centres. It is reasonable to assume that different data from people with psychosis in the same centres will be correlated and measurements on the same person even more highly correlated. To handle this data structure we will use Mixed Models (including fixed effects and random latent effects) using the appropriate model for the distribution of outcome. For the continuous scaled primary outcome WHOQoL, a linear mixed effect model will model change before and after intervention to estimate mean difference as well as the moderating effects of key health inequity measures (gender, urban/rural residence, socio-economic status) and process indicators (e.g. engagement with facility-based and community-based interventions).

The final selection of outcome measures for the evaluation will be informed by PWLE of psychosis and other stakeholders, and Theory of Change roadmaps (ToC 1; ToC 2; ToC 3; ToC5) inclusive of agreed indicators of success. Quality of life is a valued outcome for both psychosocial interventions and antipsychotic medication, and is therefore the current proposed primary outcome measure. The range of potential measures are indicated in Table 5 below with outcome measures carried out at baseline (WP3) and at 6 and 12 months (WP 4). This allows for the incorporation of other measures prioritised by PWLE and other stakeholders, such as food insecurity [42], and will give enough time for participants to engage with the innovation to investigate feasibility, fidelity, cost-effectiveness and outcomes.

**Table 5 pone.0293370.t005:** WP4 anticipated outcome measures.

**Focus**	**Measure used to capture focus**	**Baseline (WP3)**	**6 months (WP4)**	**12 months (WP4)**
Primary outcome PWLE				

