## Discussion

### Strengths and limitations

PROMISE is an innovative implementation science project designed to improve psychosis services and outcomes, and if so to understand how that was achieved. Of particular note are the principles of how we will engage with PWLE through the process, including partnership in co-design, and building networks and capacity. The psychosis awareness, diagnostic, and therapeutic materials that we develop could contribute to facilitating a contextualized roll-out of similar models of care in other LMICs in (sub-Saharan) Africa and beyond.

From the perspectives of guideline bodies that prefer efficacy to be evidenced through randomised controlled trials, the fact that we do not use this approach will be judged as the primary limitation of the work proposed. As discussed in WP4 (above), however, this would arguably be unethical where those in the control arm received no treatment at all. Our quasi-experimental sequential implementation design will allow for iteratively strengthening services and improving the intervention in each district.

There could also be tensions between an agreed research plan between ourselves and our funder, and what PWLE and others in Malawi may actually want–not least in having a specified primary outcome, to allow a power calculation, which may not be what those in Malawi value most. We acknowledge this in our ‘anticipated’ feasibility testing structure and outcome measures (see Tables 4 and 5), which are at the very least open to additions. It will be important for us to monitor and work with any tensions that arise through: regular, open, and frank engagement between researchers and other stakeholders; adjusting our workplan where feasible and if appropriate in response to external engagement; working to ensure an alignment in expectations between different stakeholders; and acting as a conduit for the communication of any concerns by PWLE to our funder and to healthcare providers.

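### Three centres are too few for a random top level in the primary WHOQoL model; district is better fitted as fixed with district by time, with HSA clustering allowed for

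*Protocol article*

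**What the plan says.** In the protocol article, WP4 Activities describes the primary analysis as follows.

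- Structure: "The data will have a three-level structure with repeated outcomes measures collected with individuals clustered within three separate assessment centres".
- Correlation: "It is reasonable to assume that different data from people with psychosis in the same centres will be correlated". No ICC is given.
- Method: "To handle this data structure we will use Mixed Models (including fixed effects and random latent effects"). The article does not list which terms are random, or say whether change may differ by centre.
- Target: "a linear mixed effect model will model change before and after intervention to estimate mean difference". Results are also to be shown descriptively for each district and for the three together.
- Sample size: "A sample size of 150 will be sufficient to detect a pre-post improvement of 20% overall (across the four sub-scales") of the WHOQoL, "with a power of 90% (alpha = 0.05"). Clustering is not mentioned.

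On delivery, WP3 Activities says: "We will train 20 HSAs in three districts (n = 60"). The section on deploying the prototype manual has the HSAs deliver the protocol. Research assistants also facilitate the psychosocial interventions.

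On roll-out, WP3 Activities takes the districts in sequence. Two took part in WP1 and WP2, and Ntcheu is new. The WP4 introduction counts iterative improvement as an advantage of the design, and Strengths and limitations describes it as "iteratively strengthening services and improving the intervention in each district".

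**The concern.** A random effect for centre asks the data to estimate a variance from three units. Such an estimate has 2 df and is often zero.

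Which centre variance matters is a separate question. The estimand is within-person change. A centre effect that shifts all scores in a district equally drops out of that change. What can affect the SE is variation between districts in the change itself. The design makes such variation plausible, because the intervention is meant to evolve from one district to the next and one district lacks the earlier engagement.

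A random intercept does not capture that variation. A random centre effect on change does, but estimates it from three units. Meanwhile the HSAs, a delivery level with enough units to model, are absent from the stated structure.

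At stake are the width of the interval for the primary outcome and the clarity of what the pooled change describes.

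**Working it through.** **Inputs.** From the article: N = 150, 90% power, alpha 0.05, 3 centres, 60 HSAs. Assumed: two-sided test, the three centres are the three districts, 50 people in each, 150/60 = 2.5 people per HSA, and all ICCs and between-district SDs. The article gives none of these.

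**1. The plan's figure.** N = 150 cannot be reproduced or refuted, because no SD or baseline mean is stated. For a paired comparison it implies a standardised change of (1.960 + 1.282)/√150 = 0.265. A 20% improvement then corresponds to an SD of change of 0.20/0.265 ≈ 0.756 of the baseline mean.

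**2. Precision of a centre variance from three units.** The moment estimate is zero when the between-centre mean square does not exceed the within-centre one. Its probability is P(F(2,147) < 1/(1 + 50·ICC/(1 − ICC))).

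| Assumed ICC | Formula | Simulation (20,000 trials) |
|---|---|---|
| 0.01 | 48% | 49% |
| 0.02 | 39% | 39% |
| 0.05 | 24% | 24% |

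Even if centre means were known without error, the 95% interval for the between-centre SD would run from √(2/χ²(0.975, 2 df)) = 0.52 to √(2/χ²(0.025, 2 df)) = 6.3 times the estimate.

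**3. Random centre intercept only.** The intercept b(centre) appears in both the before and after scores, so it cancels from the difference. In simulation the SE of mean change stayed at about 0.081 for centre intercept variances of 0, 0.3 and 3. The imprecision in step 2 therefore does not by itself harm the SE of change, and the intercept does not deal with district differences in change.

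**4. Variation in change ignored, with inference to districts in general.** Let τ be the between-district SD of change, in units of the within-district SD of change. The ICC of change is τ²/(1 + τ²), the SE ratio is √(1 + 49·ICC), and the type I error is 2·(1 − Φ(1.96/ratio)).

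- τ = 0.1: ICC 0.0099, ratio 1.22, type I error 10.8% (simulation 10.7%).
- τ = 0.2: ICC 0.0385, ratio 1.70, type I error 24.8% (simulation 25.3%).

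**5. Random centre effect on change.** With a z test, simulated type I error is 7%, 10% and 13% at ICCs of change of 0.01, 0.02 and 0.05. A t test on the three district mean changes has 2 df and a critical value of 4.30. Where 150 independent pairs would give 90% power, it has 33%, 27% and 18% at those ICCs.

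**6. HSA clustering.** The design effect is 1 + (2.5 − 1)·ICC.

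| Assumed ICC | Design effect | SE ratio | Power |
|---|---|---|---|
| 0.05 | 1.075 | 1.04 | 88% |
| 0.10 | 1.15 | 1.07 | 86% |
| 0.20 | 1.30 | 1.14 | 81% |

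With uneven caseloads (assumed CV 0.8) and ICC 0.20, the design effect is 1 + ((1 + 0.8²)·2.5 − 1)·0.20 = 1.62, an SE ratio of 1.27.

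**7. District fixed.** With equal districts, the average of the three district changes is the overall mean change. Its SE, before any HSA clustering, is the within-district SD of change divided by √150.

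**The case against.** The strongest reply is that the article never says centre is random. A fixed centre effect with a random person effect also fits its description, and the exact terms are commonly left to an analysis plan. This stands in part: the random-centre reading is the natural one, since centre is named as a level of a structure to be handled by mixed models, but it is an inference. Silence on the exact terms is not itself a fault.

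Second, the article's descriptive target is an overall figure for the three districts, and it makes no statistical claim about districts in general. If the districts are fixed, the interval is not too narrow on account of district variation, and the proposed model gives nearly the same interval (step 7). This stands. The gain lies mainly in a defined average and a stated scope.

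Third, results by district are already promised. They are descriptive only, so they neither put district by time into the model nor define the pooled estimate.

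Fourth, HSAs are not the only people who deliver care, since research assistants and facility staff contribute too, and the HSA effect is small. Both are true, but HSA clustering remains cheap to allow for.

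A reader might infer that the centre variance cannot be estimated at all, or that the SE of the WHOQoL change is shown to be unreliable. The documents support neither. The variance is poorly estimated rather than inestimable, it cancels if only the intercept is random, and the error rates in steps 4 and 5 rest on assumed variation and on an inferential target that the article does not state.

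**Conclusion.** The point holds in a limited form. Read naturally, the plan has a random top level with three units, which cannot be estimated with useful precision. If random on the intercept only, it leaves district differences in change unaddressed. If random on change, the analysis is anti-conservative with z or has very low power on 2 df.

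The type I error of about 11% to 25% is conditional on an assumed between-district SD of change of 0.1 to 0.2 and on inference beyond the three districts. It is not a property of the plan if the districts are treated as fixed. Leaving out HSAs probably understates the SE by a few per cent, and by more with a higher ICC or uneven caseloads. No single corrected sample size or power can be given, because the article states neither an SD nor an ICC. This is an inexpensive improvement that should be made, not evidence that the primary analysis fails.

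**What to change.** - Fit district as a fixed effect with district by time. Report the change in each district and their average, with the weights pre-specified.
- Limit the conclusion to these three districts as studied, with an intervention revised between them.
- Keep person as a random level. Record the HSA identifier for each participant, and allow for HSA clustering with a random effect or a cluster-robust SE with small-sample correction.
- State that the sample size of 150 at 90% power refers to the fixed-district average and makes no allowance for HSA clustering.

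The cost is a change of analysis wording and one extra identifier, best captured from the start of data collection. No further participants are needed for the change of model. The interval will be slightly wider once HSA clustering is included, and the trial gives up a statistical claim about other districts, which three units could hardly support.

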### WP4—Evaluation of the psychosis detection and management system

Given the ethical issues associated with randomised controlled trials in this context, in particular that a control group would equate to no care for some or even most people [40], we have opted for a sequential implementation (WP1, 2 & 3) and a quasi-experimental statistical evaluation of outcome (WP4). Intervention cohort studies without a control group have been shown to be beneficial when creating a control group is unethical [41]. This also has the practical advantage of allowing us to support strengthening primary care and the management by District Mental Health Teams of people with psychosis as we identify them in each district. It also allows for iterative improvement of the intervention, replicating what happens in routine settings. To address ’maturation’ effects (e.g., change in staff performance due to the evolution of clinical skills) and Hawthorne effects, we will employ a 12-month intervention and observation period. We will keep a log of any time-related changes in service delivery and integration into primary care during the process. This will allow us to closely monitor any secular trends, such as changes in local healthcare provision or MoH policies, that might impact upon delivery of intervention or outcomes. In addition, we will continue qualitative and quantitative data collection with the HSAs surveyed throughout to give us insight into potential mechanisms.

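### Engagement builds up during follow-up, so its planned moderating effect on WHOQoL change cannot be read as moderation or dose-response, and the bias can run either way

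*Protocol article*

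**What the plan says.** The WP4 Activities section describes the evaluation as an "Intervention cohort study without controls / pre-post sequential group design". For WHOQoL, "a linear mixed effect model will model change before and after intervention to estimate mean difference as well as the moderating effects" of two groups of variables. The first is "key health inequity measures (gender, urban/rural residence, socio-economic status". The second is "process indicators (e.g. engagement with facility-based and community-based interventions".

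On timing, the WP4 introduction states that "we will employ a 12-month intervention and observation period". The Activities section has "outcome measures carried out at baseline (WP3) and at 6 and 12 months (WP 4", and says that this schedule "will give enough time for participants to engage with the innovation to investigate feasibility, fidelity, cost-effectiveness and outcomes".

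Two WP3 sections bear on who engages with what. Under Evaluating impact on service utilisation, the facility to which a person with probable psychosis is referred depends on severity. Under WP3 Activities, HSAs use specialist referral routes when the presentation is complex.

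The article does not say how or when engagement is measured, and Table 5 lists no engagement measure.

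**The concern.** A moderator has to be fixed before the change that it is said to modify, or at least be unaffected by it. Gender, residence and socio-economic status can meet that condition. Engagement cannot, because it unfolds alongside the outcome.

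The dependence can arise in several ways. People who are getting better may attend more, and people who leave the area may both attend less and differ in outcome. People who are more unwell may be directed to more facility contact. The first two would make engagement look helpful, and the third could make it look useless or harmful. There is no control arm to show what high and low engagers would have done without the intervention.

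The stake is interpretation. In an uncontrolled study, a gradient of benefit with engagement is easily taken as support for a causal effect, and a reverse gradient as evidence against one. The model as described supports neither reading.

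**Working it through.** **1. Timing.** WHOQoL is taken at 0, 6 and 12 months. The intervention and observation period is 12 months, and engagement is expected to develop within it. Exposure and outcome therefore accrue together.

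**2. What the coefficient estimates.** With a single cohort, the engagement-by-time term is in essence the slope of change on engagement:

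b = ρ × SD(change) / SD(engagement)

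If engagement has no effect, ρ is the correlation between engagement and the change that would have happened anyway. Then b is zero only if ρ is zero, and it takes the sign of ρ.

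**3. The plan's own figure.** The article gives n = 150 for a 20% pre-post gain at 90% power and alpha 0.05. For a paired two-sided test the detectable change is (1.960 + 1.282)/√150 = 0.265 SD of change. No baseline mean or SD is given, so 150 can be neither reproduced nor refuted. No figure is given for the engagement analysis. The value 150 is used below only as the number analysed.

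**4. Illustration A: correlation placed on the whole observed change.** 5,000 simulated trials per row, n = 150, engagement split at the median, no engagement effect. The expected false gap between halves is 2 × 0.798 × ρ SD of change, where 0.798 is the mean of the upper half of a standard normal.

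| ρ (assumed) | False gap, SD of change | Significant at 5% |
|---|---|---|
| 0 | 0 | 4.9% |
| 0.1 | 0.16 | 16.6% |
| 0.2 | 0.32 | 51.1% |
| 0.3 | 0.48 | 85.8% |

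A repeat run gave 49.5% and 85.3% for the last two rows.

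**5. Illustration B: correlation placed on true change in months 0-6 only, with measurement error.** 4,000 simulated trials per row, n = 150, engagement continuous in the test. All inputs are assumed: baseline mean 50, between-person SD 15, error SD 7, spontaneous gain 5 points over 12 months, SD 7 for each 6-month gain.

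| Correlation (assumed) | High-minus-low gap, points | Significant at 5% | Overall mean change |
|---|---|---|---|
| −0.5 | −5.6 | 88% | 5.0 |
| −0.3 | −3.2 | 44% | 5.0 |
| 0 | 0.0 | 6% | 5.0 |
| 0.2 | 2.2 | 23% | 5.0 |
| 0.3 | 3.3 | 45% | 5.0 |
| 0.5 | 5.5 | 88% | 5.0 |

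**6. Why A and B differ.** In B the SD of observed change is √(7² + 7² + 7² + 7²) = 14, and true 0-6 month change correlates 7/14 = 0.5 with it. Correlations of 0.2 and 0.3 therefore act as 0.10 and 0.15 on observed change. As a check, atanh(0.10) × √147 = 1.22 and atanh(0.15) × √147 = 1.83. Against 1.96 these give about 23% and 45%, as simulated. A and B are two readings of one mechanism, so the result is a range: about 23% to 51% at 0.2 and 45% to 86% at 0.3.

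**7. The mean difference.** The marginal mean change in B stays at 5.0 in every row. The time coefficient of a model with an engagement-by-time term is another quantity: the change at the reference engagement level. With equal halves and low engagement as reference it equals the overall change minus half the gap. For an assumed overall change of 0.30 SD:

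- ρ = 0.2: 0.30 − 0.32/2 = 0.14 SD
- ρ = 0.3: 0.30 − 0.48/2 = 0.06 SD
- ρ = −0.2: 0.30 + 0.32/2 = 0.46 SD

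If engagement is centred, or the result is averaged over the sample, the overall mean is recovered.

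**The case against.** The strongest reply is that this is a secondary use of the model, given as an example in a condensed article, and that coding and measurement belong in an analysis plan that is not shown. Part of this stands. How engagement is scored, how the model is parametrised and which coefficient is reported may all be settled elsewhere, and none of that is counted here as missing. What the article does state is that engagement is a moderator in the model for the primary outcome, on the same footing as baseline traits. That choice is open to comment.

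The simulations can also be called circular: they assume a correlation and then show how often 150 people would detect it. That is fair. They show how easily a modest dependence becomes a significant result, not that the dependence exists.

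A reader might draw three stronger conclusions, and the documents support none of them.

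- **That the bias favours the intervention.** The direction is open. Referral by severity and complexity makes it plausible that people with a worse outlook have more facility contact, which would push the estimate the other way.
- **That the engagement term credits the intervention with improvement of any cause.** That follows from the uncontrolled pre-post design, which the article discloses and defends ("Intervention cohort studies without a control group have been shown to be beneficial" when a control group would be unethical). The engagement term adds a separate problem, a false gradient.
- **That the primary mean difference is biased.** The article names the mean difference and the moderating effects as separate quantities. The mean is at risk only under one way of coding and reporting the model.

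The article also does not say that the engagement result will be presented as proof of effect.

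**Conclusion.** The point holds in a limited form. The plan treats a variable that arises during follow-up as a moderator of change over the same period, in a cohort without controls. The resulting coefficient cannot be interpreted as moderation or dose-response, whichever sign it takes. The secular-change log and the 12-month period described in the WP4 introduction do not address this dependence.

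If the correlation between engagement and spontaneous change is 0.2 to 0.3 in absolute size, a nominal 5% test would be significant in roughly 23-51% to 45-86% of trials with no engagement effect. The range reflects measurement error, timing and how engagement is coded. The correlations, SDs and mean gain are assumptions, and all 150 people are taken to be analysed. The overall pre-post mean change is unaffected, provided it is not read off at a reference level of engagement.

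**What to change.** 1. In the primary WHOQoL model, keep only baseline variables as moderators, and take the mean difference from a model without engagement.
2. Move engagement to a separate secondary analysis, labelled as an association with no causal reading.
3. Preferably order it in time: relate engagement in months 0-6 to WHOQoL change from 6 to 12 months, adjusted for baseline and 6-month WHOQoL. Table 5 schedules WHOQoL at all three times. Engagement might be derived from the service contacts that the Economic analysis section has patients report at each data-collection point.

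The cost is mainly a change of wording. The time-ordered analysis uses one interval, so it is less precise. It also omits any benefit gained in the first six months, and it conditions on a 6-month score that engagement may already have influenced, so it answers a narrower question. It further requires that engagement can be derived from the contact data, which are reported retrospectively and collected for costing. If it cannot, a measure of engagement has to be added, or the result kept purely descriptive.
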